### Outcome Measures

The primary outcome measure is depressive symptomology, which is being measured using the Edinburgh Postnatal Depression Scale [32]. Secondary outcome measures to assess maternal functioning include: Hospital Anxiety and Depression Scale [33], Parenting Sense of Competence Scale [34], Dyadic Adjustment Scale [35], Emotional Support Questionnaire [36] and Self-Efficacy [37]. The Care Index [38] is being used to assess the interaction between the mother and baby. Maternal perceptions of the telephone peer-support and are being assessed using the Peer-support Evaluation Inventory.

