### Development of Mums4Mums: telephone peer-support for mums experiencing PND

The current proposal has adapted for use in the UK a telephone-based peer-support intervention shown to be effective in Canada [23], to pilot its use, and provide preliminary data on its effectiveness in reducing depressive symptoms amongst women experiencing PND.

The proposal builds on an exploratory study that examined a range of stakeholder's views about the need for, and potential acceptability of, a telephone-based peer-support intervention, their views about the potential impact of the intervention, and how it would fit into current practice. General Practitioners (GPs) (n = 6), health visitors (n = 7) and mothers who had recovered from PND (n = 10) were interviewed and the results indicated that stakeholders perceived a need for a telephone-based peer-support intervention for women currently experiencing PND in the UK. It was suggested that this would represent an additional resource for mothers, and that a telephone-based intervention would be acceptable due to its flexibility and use of non face-to-face contact.

The Mums4Mums telephone support intervention was piloted with women currently living with PND (n = 8). The pilot study was conducted to explore key elements of the telephone based peer-support intervention such as training, acceptability, and recruitment. In-depth interviews were again conducted, and the initial findings suggested that the Mums4Mums intervention was acceptable and potentially beneficial in supporting women with PND.

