### Mums4Mums Feasibility Trial

The current study aims to test the feasibility of conducting a large-scale randomised controlled trial of a telephone based peer-support intervention to reduce depressive symptomology in women with PND.

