### Research Objectives

The objectives of the feasibility study are to:

i) ascertain the acceptability of a randomised control trial for women with PND;

ii) explore effective methods of recruitment;

iii) explore the participants' and health professionals' views about the intervention;

iv) ascertain the acceptability of the outcome measures;

v) identify a cost-effectiveness measure;

vi) provide an estimate of the size of change that might be expected with such an intervention to inform the power calculation for the larger RCT;

vii) build a working alliance with health care professionals for the larger clinical trial;

viii) make any necessary adaptations to the intervention and develop a full proposal for a main RCT to be submitted to the MRC in 2012.

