### Data Analyses

#### i) *Quantitative*

Descriptive methods will be used to describe participant characteristics, to compare the 'refusers' with the study participants, and to report levels of participation and drop out. Comparison of intervention and control group outcome data will be provided with regard to the outcome measures described above. The results of the statistical analyses will be used to reach some preliminary conclusions regarding the viability and acceptability of the intervention, the usefulness of the outcome measures being used, and the sample size required in a full trial.

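### The trial's aim is feasibility, but its only primary outcome and its sample size are framed as an efficacy test on the EPDS that 30 women cannot support

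*Protocol article*

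**What the plan says.** Four parts of the protocol article bear on this.

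- **Aim.** The Mums4Mums Feasibility Trial section states: "The current study aims to test the feasibility of conducting a large-scale randomised controlled trial".
- **Objectives.** Research Objectives lists eight. They include to "ascertain the acceptability of a randomised control trial for women with PND" and to "ascertain the acceptability of the outcome measures"; others cover recruitment methods, stakeholder views, a cost-effectiveness measure, working relationships and the main-trial proposal. The sixth alone concerns the effect on symptoms: to "provide an estimate of the size of change that might be expected with such an intervention to inform the power calculation".
- **Primary outcome and size.** Outcome Measures states: "The primary outcome measure is depressive symptomology, which is being measured using the Edinburgh Postnatal Depression Scale". The abstract agrees. The Sample Size section justifies 30 participants by 80% power, two-sided, for an effect of about 0.6 SD.
- **Use of the results.** The quantitative part of Data Analyses describes refusers, participation and drop-out, then the comparison of outcomes between arms. It then says: "The results of the statistical analyses will be used to reach some preliminary conclusions regarding the viability and acceptability of the intervention". The same sentence adds the usefulness of the measures and the sample size for a full trial.

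**The concern.** The aim, the primary outcome and the sample-size rationale do not fit together. The aim concerns whether a large trial can be run. The one outcome given primary status, and the only justification for 30 women, belong to a test of whether the intervention works. None of the eight objectives asks for that test; the sixth asks for an estimate. Recruitment, refusal, retention and completion have no primary status, although they bear most directly on the aim.

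The primary outcome normally leads the report. A trial that recruited and retained well but showed no significant EPDS difference could be presented as negative. One that recruited poorly but showed a chance difference could be presented as support for the main trial. Neither reading follows from a feasibility aim.

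**Working it through.** **Inputs.** Total 30, effect 0.6 SD, power 80%, two-sided (Sample Size section). The stated level of 95% is read as alpha 0.05. The allocation ratio is not given in the article; 1:1 is assumed, so 15 per arm.

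**1. The plan's own figure.** For two independent means, n per arm = 2 × (1.960 + 0.842)² / 0.6² = 43.6, so 44 per arm and 88 in total. The stated 30 is not reproduced. A one-sided test needs 35 per arm (70 in total). Reading 30 as per arm gives 64% power.

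**2. Power at 15 per arm.** The standard error of the standardised difference is √(2/15) = 0.365. The expected z is 0.6 / 0.365 = 1.643. Power = Φ(1.643 − 1.960) ≈ 0.38; the noncentral t gives 0.35. If the true effect were 0.6 SD, the comparison would be non-significant about 62–65% of the time. The effect detectable with 80% power is 2.802 × 0.365 = 1.02 SD (1.06 by t).

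**3. Precision for the sixth objective.** The 95% half-width is 1.960 × 0.365 = 0.72 SD, or 2.048 × 0.365 = 0.75 SD by t. Either exceeds the 0.6 SD target.

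**4. Sensitivity to baseline adjustment.** The article states neither an adjustment nor a correlation r, so r is an assumption. Variance is multiplied by (1 − r²).

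| Assumed r | Total N for 0.6 SD, 80% power | Effect detectable with 30 women |
|---|---|---|
| 0.3 | 80 | 0.98 SD |
| 0.5 | 66 | 0.89 SD |
| 0.7 | 46 | 0.73 SD |
| 0.8 | 32 | 0.61 SD |

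At r = 0.5 the half-width is 0.72 × √0.75 = 0.62 SD (normal), still slightly more than the target. A total of 30 is reached only at r of about 0.81.

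**5. What 30 women can say about feasibility.** These retention counts are illustrative assumptions, with exact (Clopper-Pearson) 95% CIs: 24/30 = 80% gives 61% to 92%; 27/30 = 90% gives 73% to 98%. A single arm is rougher: 12/15 = 80% gives 52% to 96%. These intervals are wide, but they address the stated aim directly.

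**The case against.** The strongest case on the other side is that the EPDS comparison has a proper place and that feasibility is covered elsewhere. Much of that stands.

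- A reader might infer that the primary outcome answers a question outside the eight objectives. It does not: the sixth asks for the size of change, and the section on the development of Mums4Mums names a purpose to "provide preliminary data on its effectiveness in reducing depressive symptoms amongst women experiencing PND". The mismatch lies in the primary status and the testing frame; collecting and estimating EPDS is sound.
- A reader might infer that nothing collected addresses feasibility or acceptability. That is also too strong. Outcome Measures includes the Peer-support Evaluation Inventory, Process Data plans stakeholder interviews on acceptability and feasibility, and Data Analyses reports participation and drop-out. None of these has primary status, and the inventory and interviews concern the intervention more than the conduct of a trial.
- A reader might infer that acceptability will be judged from the EPDS difference. The text permits this reading but does not require it. The same paragraph also covers participation and drop-out, and the conclusions are called preliminary. The wording simply does not say which result supports which conclusion.
- No section makes the main trial conditional on a significant EPDS result, so the misreadings described above are risks of presentation and not planned decision rules.
- Thresholds for proceeding to a main trial do not appear in the article. They may sit in the full protocol, and their absence is not counted here.

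**Conclusion.** The point holds as a mismatch within the stated design. A feasibility trial gives sole primary status to an efficacy measure and justifies its size by hypothesis-test power, while the only objective tied to that measure asks for estimation. The test cannot carry that weight: power at 0.6 SD is about 35–38%, and the 95% half-width is 0.72–0.75 SD.

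These figures assume 1:1 allocation, alpha 0.05, an unadjusted comparison and no drop-out. Drop-out would worsen them. Baseline adjustment would improve them, but only a correlation of about 0.8 would bring the stated power within reach. The mismatch itself does not depend on these assumptions. It should be corrected because it could mislead the reading of the trial, although it does not invalidate the data.

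**What to change.** 1. **Outcome Measures.** Give primary status to feasibility measures that the plan already reports or that follow directly from its data collection: participation and refusal, drop-out, and EPDS completion at 4 months by arm. Give each a 95% CI. Report participation by recruitment route, and as a proportion of eligible women only where that denominator is known. Recruitment also allows self-referral by leaflet and website and referral from a waiting list, so the denominator is clearest for women screened by health visitors. Call uptake could be added only if calls are recorded against a stated plan; the article gives no planned number.
2. **EPDS.** Keep it as the candidate primary outcome for the main trial, reported as a between-arm difference with 95% CI and no efficacy test. This is what the sixth objective needs.
3. **Sample Size.** Replace the power statement with the precision that 30 women give for the feasibility proportions and for the EPDS difference.
4. **Data Analyses, quantitative part.** State that viability and acceptability rest on participation and drop-out, the Peer-support Evaluation Inventory and the stakeholder interviews. State that the outcome comparison informs only the main-trial sample size and the usefulness of the measures.

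The cost is wording, plus some care in recording denominators by route. The real concession is giving up a headline efficacy test, which a trial of this size could not support.

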### Process Data

In-depth, semi-structured interviews will be conducted with a random sample of all stakeholders to establish the acceptability and feasibility of the intervention for participants, peer-supporters and health visitors.

### Cost-Effectiveness

A prospective economic evaluation is being conducted. The focus is on the additional costs of delivering the training programme for the services involved. The costs of training will be calculated using a record of the resources employed. Unit costs for service delivery will be taken from a national compendium (e.g. costs of training and supervision) and multiplied by the intensity of the service used by each family. A 'Service Use' Questionnaire is being used to collect data on public service utilisation by study participants. Unit costs will be obtained from national databases. Training, delivery and service utilisation costs will be combined to provide an estimate of the total health and social care cost in each arm. The expected incremental cost-effectiveness ratio for peer-support vs. usual care in the prevention of PND cases will be estimated. A within-trial probabilistic sensitivity analysis will be undertaken using non-parametric bootstrap method. The results will be presented as ICERs and cost- effectiveness acceptability curves. Scenario analyses will be used to examine the impact of differential training and resourcing models on the expected cost-effectiveness. The data collected in the trial will be used to inform pre-trial modelling as part of the design process for a future full scale RCT with economic evaluation.

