### Inclusion criteria

#### Inclusion criteria

women >16 years of age at the time of giving birth and who are experiencing depressive symptomatology (i.e. EPDS > = 10 and/or clinical judgment) at or after the 8-week check, and who are potentially receptive to receiving telephone support.

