### Recruitment

All health visitors within Coventry and Warwickshire Care Trusts (PCTs) are recruiting to the study. Potential participants are screened for eligibility by the health visitors at the 8-week postnatal check using either the Edinburgh Postnatal Depression Scale (EPDS > = 10) or the three Whooley questions recommended by NICE [13]. Eligible women are then given a brief information leaflet about the study, and women who would like further information are asked for their written consent for the health visitor to give their contact details to the research team.

In addition to the recruitment method outlined above, the study information leaflet is available within GP surgeries and Children's Centres within Coventry and Warwickshire allowing participants to self-refer into the study by contacting the research team directly. Participants can also access information about the study using the link at 'Netmums' or via the Warwick University webpage. Eligible patients are also being referred to the study from the 'Improved Access to Psychological Therapies (IAPT) waiting-list.

Following referral to the study team, a researcher sends a full information sheet and contact with the mother is arranged two weeks later, to discuss her participation. Once a participant has agreed to take part and provided consent, their details are passed onto the Clinical Trials Unit at the University of Warwick for randomisation. The group allocation information is provided to the researcher who then informs the participant.

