### Intervention group

All participants receive standard care from their GP and health visitor. Women allocated to the intervention group also receive telephone support calls over a period of 4 months from peer-supporters who have been specially trained to deliver the intervention (i.e. the same peer-supporters that delivered the pilot study intervention). Outcome measures tested in the pilot phase are being collected at baseline, 2- and 4-months.

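### The cost-effectiveness ratio is stated per PND case prevented, but the trial treats women who already have depressive symptoms and lists no incident-case outcome

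*Protocol article*

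**What the plan says.** The Cost-Effectiveness section plans a prospective economic evaluation that combines training, delivery and service-use costs in each arm. It names the effect in one sentence: "The expected incremental cost-effectiveness ratio for peer-support vs. usual care in the prevention of PND cases will be estimated". It continues: "The results will be presented as ICERs and cost- effectiveness acceptability curves". A non-parametric bootstrap is planned, and the data are to inform modelling before a full-scale trial.

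Other sections describe the population and the outcomes:

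- **Aim** (Mums4Mums Feasibility Trial): a "telephone based peer-support intervention to reduce depressive symptomology in women with PND".
- **Eligibility** (Inclusion criteria): women "who are experiencing depressive symptomatology (i.e. EPDS > = 10 and/or clinical judgment) at or after the 8-week check".
- **Screening** (Recruitment): "using either the Edinburgh Postnatal Depression Scale (EPDS > = 10) or the three Whooley questions recommended by NICE".
- **Primary outcome** (Outcome Measures): "The primary outcome measure is depressive symptomology, which is being measured using the Edinburgh Postnatal Depression Scale". The other listed measures cover anxiety and depression, parenting competence, dyadic adjustment, support, self-efficacy, mother-baby interaction and perceptions of the peer support.
- **Timing** (Intervention group): "Outcome measures tested in the pilot phase are being collected at baseline, 2- and 4-months".
- **Objective (v)** (Research Objectives): to "identify a cost-effectiveness measure".

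**The concern.** A ratio per case prevented belongs to a trial in women who are at risk but not yet ill. The article itself draws this line: the section The Evidence describes the Canadian telephone pilot as enrolling women at high risk of depression. The present trial requires symptoms at entry and aims to reduce them. An economic result labelled as prevention would attach a benefit to the intervention that this design does not estimate.

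What is at stake is the input to the main trial. A model of prevention starts from women without the condition and applies a reduced incidence. A model of treatment starts from women with the condition and applies a faster or more frequent recovery. An estimate of the second kind that carries the label of the first could be put into the wrong part of the model. The economic section also appears to settle an effect unit that objective (v) treats as still to be found.

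**Working it through.** The article gives no value for the ratio, its numerator or its denominator, so there is no figure to reproduce. The check is whether the stated effect can be obtained from this population and these outcomes.

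**Formula.** ICER = ΔC / ΔE, where ΔC is the between-arm difference in mean cost and ΔE is the between-arm difference in mean effect. The planned acceptability curve gives, for each threshold λ, the probability that λ × ΔE − ΔC is above zero. Everything depends on what ΔE is.

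**Reading 1: prevention means first onset.** The women at risk would be those without the condition at entry. Eligibility requires depressive symptoms, by EPDS of 10 or more and/or clinical judgment, and the aim refers to women who have PND. No listed outcome records onset or diagnosis. ΔE then has no meaningful content. If ΔE is set to 0, the ratio cannot be formed and λ × ΔE − ΔC reduces to −ΔC for every λ. The acceptability curve is then flat and reports only whether peer support costs less.

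**Reading 2: prevention means fewer women who are cases at follow-up.** ΔE is then the between-arm difference in the proportion of women below some EPDS threshold at 2 or 4 months. EPDS is collected at both times, so this can be computed. But every woman had symptoms at entry, so the quantity is recovery. The label is wrong even though the number exists.

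**Reading 3: the effect is the primary outcome itself.** ΔE = (mean 4-month EPDS under usual care) − (mean 4-month EPDS under peer support), adjusted for baseline EPDS. A positive value favours peer support. This uses the trial's own primary measure and needs no case definition, but it is not what the sentence says.

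| Reading | Obtainable from the listed outcomes? | Matches the word prevention? |
|---|---|---|
| First onset | No | Yes |
| Non-case at follow-up | Yes | No, it is recovery |
| EPDS points | Yes | No, it is symptom reduction |

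No row has yes in both columns. The sentence in the Cost-Effectiveness section therefore cannot be followed as worded and also agree with the eligibility criteria, the aim and the outcome list.

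**The case against.** The strongest reply is that the phrase is loose wording for cases averted at follow-up, and that an analyst would compute this from EPDS without difficulty. That stands in part: it makes the ratio computable. It does not rescue the wording, because the quantity obtained is recovery in a treated population.

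A second reply is that a journal article condenses a fuller protocol, which may define a case and a time point. This stands. The absence of a follow-up threshold here is not a finding. The finding rests on what the article does state, an effect that conflicts with its own population, aim and outcomes.

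A third reply is that the economic work is exploratory: objective (v) leaves the measure open, and cost, service-use and EPDS data are collected whatever the label. This also stands, and it limits the severity.

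Two stronger readings are tempting:

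- A reader might infer that the ratio is simply undefined because none of the 30 women could become a case. That holds only if prevention must mean first incidence, and the article does not say so.
- A reader might infer that the small sample makes the ratio unusable because the effect difference could fall on either side of zero. That is imprecision from a sample of 30, and it would affect any effect unit. The acceptability curves already planned stay defined when the effect difference crosses zero.

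It might also be argued that women admitted on clinical judgment with EPDS below 10 would count as successes from the start. Randomisation balances them between arms in expectation, so they would dilute the contrast rather than bias it.

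**Conclusion.** The point holds in limited form. The effect unit of the cost-effectiveness ratio is wrong as written for a treatment trial in women who already have symptoms, and no incident-case outcome is listed. Under the literal reading there is no meaningful effect difference. Under the charitable reading the result is a cost per recovery presented as a cost per case prevented.

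Severity is moderate. The defect lies in one phrase of an exploratory component, it does not touch the primary comparison or data collection, and it can be corrected before analysis. It matters because the section sends these results forward to modelling for the main trial. No numerical size is attached: the documents give no event rates or costs from which one could be derived. The conclusion needs no assumption about rates, allocation ratio or sample size. It rests only on the article's statements of population, aim and outcomes.

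**What to change.** In the Cost-Effectiveness section, replace the words about preventing PND cases with an effect that the trial measures:

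1. **Main measure:** incremental cost per one-point between-arm difference in 4-month EPDS, adjusted for baseline EPDS, in all randomised women.
2. **Optional second measure:** incremental cost per additional woman with EPDS below 10 at 4 months, in all randomised women. The value 10 is the trial's own entry cut-off. Restriction to women at or above 10 at baseline should be a sensitivity analysis only, because it leaves out randomised women and the Sample Size section commits to intention-to-treat.
3. **Reconcile with objective (v):** state that these are candidate measures for the main trial, so that the economic section no longer appears to have settled what the objective leaves open.

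The cost is a change of wording. EPDS is already collected at baseline and 4 months, so no further data, visits or participants are needed. The planned bootstrap and acceptability curves can stay as they are.
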